### Sample Size

The sample size is determined based on an a priori analysis of group-specific intervention effects. This analysis is modeled as the interaction of the within-subject factor of time (preintervention vs postintervention assessment) and the between-subject factor of the group (SCM vs MM vs control). Power analysis is conducted using the G*Power software app developed by Heinrich-Heine-Universität Düsseldorf Institut für Experimentelle Psychologie to estimate how much power would be required to find small interaction effects. In this study, the intervention effect size is assumed to have weak interaction effects (Cohen *F*=0.15) based on previous research [81]. Repeated measures scores are also expected to have a moderate to strong correlation of 0.5. To achieve 80% power, 37 participants are required in each arm (SCM, MM, and control). Expecting approximately 40% attrition based on similar previous studies [82,83], we will include 200 participants and assign 67 participants to each of the 3 arms.

### Recruitment

Recruitment will be conducted via a recruitment website for psychology experiments and through the website of our laboratory. Information about the study is available via posters on those websites. The posters also contain contact information for the research team, who can be contacted directly.

### Assignment of Interventions: Allocation

Randomization will be performed after obtaining informed consent and screening the participants. It will be computerized and independently carried out by research staff using a blocked randomization scheme (block size 15) to ensure the seamless participation of those who apply to participate in the study. Eligible participants will be randomized into the SCM, MM, or waitlist group in a ratio of 1:1:1.

Participants are assigned to either the intervention (SCM or MM) or control (waitlist) condition immediately after randomization. The intervention will begin approximately 1 week after allocation. No specific instructions are given to the waitlist group, and they will be asked to wait for 4 weeks.

Interested candidates will be asked to confirm their consent to participate in this study and complete a screening questionnaire via web forms. The screening questionnaire consists of the K6 and items based on the inclusion criteria. Participants who meet the inclusion criteria are immediately included in the blocked randomization scheme and assigned by the research staff. After the participants have been assigned, they will receive an email with instructions to participate or wait.

### Assignment of Interventions: Blinding

It is practically impossible to blind the allocation in this study because the participants engage in the meditation independently, following a guide. Therefore, this study will be an open-label RCT. Once a participant is assigned to a condition, there will be no further interaction with the research staff, except when the participant contacts the research staff. To minimize interaction between the participants and research staff, notifications and instructions will be sent to the participants via automated emails. Participants can infer which group they have been allocated to, based on the instructions, but they are not explicitly informed about the groups to which they are assigned.

### Data Collection and Management

The participants will be assessed for outcome measures via web forms at baseline (pretreatment assessment) and 1 month and 2 months after the course starts (posttreatment assessment and follow-up assessment, respectively). Additionally, the participants will complete weekly and daily assessments during their courses. As mentioned earlier, the weekly measures consist of 1 question from the Affect Grid [77] and 20 questions from the PANAS [78,79]. The daily assessment involves the degree of participants’ relaxation [80] and objective physiological measures (HR and HRV) on the smartphone app. Participants will be asked to perform daily assessments using the smartphone app before and after daily meditation. The weekly assessment will be measured via web-based forms once a week immediately after the 7-day meditations, and participants will receive an email requesting them to respond to the questionnaire and a reminder to use the self-care app. The web-based survey to be conducted in this study is designed with reference to the CHERRIES (Checklist for Reporting Results of Internet E-Surveys) checklist to ensure a complete description of web-based surveys (Multimedia Appendix 2) [84]. When reporting the results, we will provide a detailed report of what is described in CHERRIES.

HR and HRV measurements will be taken on the smartphone app used for the intervention. Participants will be provided a sample and instructed to gently press their index finger against their smartphone’s camera for 30 seconds. At this time, the smartphone’s flash will turn on. By capturing the finger illuminated by the flash with the smartphone camera, HR and HRV will be measured. The procedure was set up based on a study that used HR and HRV measurements to evaluate the effectiveness of psychological interventions similar to this study [81]. HR and HRV will be measured using contact photoplethysmography, which is a noninvasive and convenient optical biomonitoring technique used to detect pulsatile changes in blood volume that appear in the microvascular bed of tissues [85]. The contact photoplethysmography method uses a white LED flashlight built into a smartphone and a rear camera to illuminate the skin for 30 seconds and detect light absorption due to arterial pulsation in the finger pad (Multimedia Appendix 3). For measuring HRV, the root mean square of successive differences—a measure of the square root of the mean squared difference between consecutive normal heartbeats—is used. The average HR measured in beats per minute is analyzed for HR.

When participants do not answer a questionnaire (baseline, preintervention assessment, and postintervention assessment), they will receive automatic reminders via email 6 days later. Participants who do not respond at baseline and preintervention assessment will receive further reminders after 13 days. If the participants are found not to respond to the questionnaire, they will be considered dropped by 14 days at baseline and preintervention assessment and by 7 days at postintervention assessment.

The data collected through the web-based forms are stored on a secure server with restricted access at the University of Tokyo. After data collection, this study will use a study-generated identification for data management, analysis, and publication. The list linking identifications to the participants’ personal information is stored on a hard disk disconnected from the internet, and the hard disk is kept in a locked cabinet.

This study will be conducted according to the protocol approved by the ethics committee of the institution to which the research team belongs. Identifications are used only for data management, and collected data and personal information are stored separately. Participants are informed that their personal information will remain confidential if they provide informed consent.

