### Interventions

SCM and MM were set as the intervention conditions and waitlist as the control condition, and the 3 groups were compared. Participants assigned to the SCM and MM groups will use a smartphone app to engage in guided meditation on their own once a day (Multimedia Appendix 1). The duration of all intervention conditions is 4 weeks. Both SCM and MM interventions contain elements of mindfulness. The difference between SCM and MM is the content of meditation in weeks 3 and 4: in SCM, participants will engage in loving-kindness meditation in weeks 3 and 4, whereas in MM, they will participate in a breath, sound, and body meditation. The duration of guided meditation is the same in both groups. Participants assigned to the waitlist group will receive no intervention during the 4-week waiting period; after the waiting period, they will be randomly assigned to either the SCM course or MM course to engage in 4 weeks of guided meditation.

The SCM and MM courses will be delivered via a smartphone app developed by the authors’ research team. Each course will offer 3 modules of guided self-help meditations. The modules in the SCM and MM courses will be structured as psychoeducation and guided meditation. The audio script for guided meditation is a Japanese version available from the University of California, Los Angeles Mindful Awareness Research Center [38], and audio instructions will be given before and after the meditation. The contents of psychoeducation include stress and stress responses and the theory of mindfulness and self-compassion. Both courses will involve the same guided meditations in weeks 1 and 2. The guided meditations contained in each week’s module are as follows (Table 1): week 1 (SCM and MM courses): a breathing meditation (7 minutes); week 2 (SCM and MM courses): a short body scan (6 minutes); and weeks 3-4: (SCM course): a loving-kindness meditation (12 minutes), including the contents of self-kindness and common humanity, and (MM course): a breath, sound, body meditation (12 minutes). Participants will receive weekly reminders via email to encourage involvement; however, there will be no minimum time commitment to participate.

**Table 1 table1:** Schedule of procedures.

Process or assessment		Screening period	Pretreatment assessment (baseline)	Intervention period					Posttreatment assessment		Waitlist intervention period					Follow-up assessment
				Wk 1	Wk 2	Wk 3	Wk 4			Wk 1		Wk 2	Wk 3	Wk 4		

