**Weekly assessment**																
	Affect Grid			✓^n^	✓^n^	✓^n^	✓^n^			✓^o^		✓^o^	✓^o^	✓^o^		
	PANAS^p^			✓^n^	✓^n^	✓^n^	✓^n^			✓^o^		✓^o^	✓^o^	✓^o^		

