#### Positive and Negative Emotions

The Positive and Negative Affect Schedule (PANAS) is used to measure the degree to which participants experienced positive and negative emotions within the past week [78]. The PANAS includes 20 items (10 positive and 10 negative emotions) that are rated on a 5-point Likert scale ranging from 1=not at all to 5=extremely. The Japanese version of this scale has demonstrated high reliability and validity [79].

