### Participant Timeline

Participants who agree to participate in the study with informed consent and meet the inclusion criteria are assigned to the SCM, MM, or waitlist group. Participants are not notified as to which group they are assigned. All participants will then receive a web-based pretreatment assessment questionnaire at baseline via email and will be asked to complete it. Simultaneously, the participants assigned to the active arm (SCN and MM) will be asked via email to download and start using the smartphone app used for the intervention. Four weeks after the start of app use, participants will be sent a web-based posttreatment questionnaire by email and asked to complete it. Participants in the waitlist group will receive a web-based posttreatment questionnaire 4 weeks after they respond to the initial baseline questionnaire. Participants in the waitlist group will be asked to download and start using the smartphone app via email, distributed with the posttreatment questionnaire. All the participants in the waitlist group will be randomly assigned to the SCM and MM groups. During the 4-week intervention, all participants will be asked to respond to daily and weekly assessments of the smartphone app. Table 1 presents the schedule of procedures.

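### PANAS and the Affect Grid are first taken after a week of meditation, so neither scale has a pre-course value in any arm

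*Protocol article*

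**What the plan says.** All references are to the protocol article.

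- **Timing.** Data Collection and Management says of the weekly form: "The weekly assessment will be measured via web-based forms once a week immediately after the 7-day meditations". The same section ties it to each person's own course: "Additionally, the participants will complete weekly and daily assessments during their courses". Participant Timeline agrees: "During the 4-week intervention, all participants will be asked to respond to daily and weekly assessments of the smartphone app".
- **Content.** The weekly form holds one Affect Grid question and 20 PANAS questions (Data Collection and Management).
- **Recall.** PANAS measures "the degree to which participants experienced positive and negative emotions within the past week". The Affect section states no recall period for the Affect Grid.
- **Table 1.** K6 and the rest of the main battery are ticked at baseline, posttreatment and follow-up. In the block headed "Weekly assessment", both affect scales are ticked only in weeks 1-4 of the intervention period (footnoted to SCM and MM) and weeks 1-4 of the waitlist's later course (footnoted to the waitlist).
- **Course content.** Meditation starts in week 1. Interventions says of SCM and MM: "Both courses will involve the same guided meditations in weeks 1 and 2". They differ only in weeks 3 and 4.

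**The concern.** A scale meant to follow affect from week to week needs a starting point that treatment has not touched. Here the first PANAS score describes a week already spent meditating, and the first Affect Grid rating comes at the end of that week. The gap is present within each arm, so it is distinct from the absence of affect ratings in the waitlist during its wait. Heart rate, heart rate variability and relaxation are better placed: they are taken before and after each meditation, so they have a day-1 value that precedes practice.

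Three things are at stake.

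1. If week 1 is used as the starting point, whatever benefit arrived in the first week becomes part of the reference. A course that works quickly would look as if it did nothing.
2. No pre-course affect score exists to use as a covariate.
3. About 40% attrition is expected (Sample Size). Anyone who leaves before the first weekly form contributes nothing on these scales, not even a starting value for a missing-data check.

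**Working it through.** The plan gives no figure of its own for change in affect. The check is therefore a reading of the schedule, followed by a calculation under assumed time courses.

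**Step 1: count the pre-course values.** By column position in Table 1, K6 has three ticks: baseline, posttreatment and follow-up. PANAS and the Affect Grid have eight each: four in the intervention period and four in the waitlist's later course. Neither has a tick at screening, baseline, posttreatment or follow-up. Scheduled pre-course affect values are thus 0 in SCM, 0 in MM and 0 in the waitlist.

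The text and the table agree, so a broken table does not explain the empty cells. Data Collection and Management does say that outcome measures are taken at baseline, but it then introduces the weekly measures separately, as an addition during the courses. The mention of all participants in Participant Timeline does not add waitlist ratings during the wait either, because the Table 1 footnotes place those ratings in the waitlist's own course.

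**Step 2: what week 4 minus week 1 would recover.** Let E1 and E4 be the effect contained in the week-1 and week-4 scores, as a percentage of the full effect. The share of the week-4 effect that is recovered is

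R = (E4 − E1) / E4.

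The documents give no time course. The three below are assumptions chosen to show the range.

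*PANAS, past-week recall, taken as the average over each week:*
- Linear rise from 0 to 100% over 4 weeks: weekly averages are 12.5, 37.5, 62.5 and 87.5. R = (87.5 − 12.5) / 87.5 = 75 / 87.5 = 0.857, or 86%.
- Rise from 0 to 100% over days 0 to 3.5, then flat: the week-1 average is 0.5 × 50 + 0.5 × 100 = 75, and week 4 is 100. R = (100 − 75) / 100 = 25%.
- Immediate and sustained: week 1 and week 4 are both 100. R = 0%.

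*Affect Grid, if read as a momentary rating at the end of each week:*
- Linear rise: values are 25, 50, 75 and 100. R = (100 − 25) / 100 = 75%.
- Complete by mid-week 1: R = (100 − 100) / 100 = 0%.
- Immediate: R = 0%.

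**Step 3: what is unaffected.** SCM and MM are randomised against each other, so their weeks 3-4 scores can be compared without a baseline. The guided meditations are the same through week 2, so early benefit common to both courses is not part of that contrast, and the week-2 score precedes any difference in content.

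**The case against.** The strongest reply accepts the schedule and disputes the consequence.

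- **The scales are peripheral, and no stated analysis fails.** This stands. PANAS and the Affect Grid sit in their own weekly section, outside the listed primary and secondary outcomes. The article nowhere explicitly promises a pre-post analysis of them. A reader might infer that affect was meant to show how the courses work. The documents do not support that: the Background, the Objectives and Strengths and Limitations tie mechanism to heart rate and heart rate variability.
- **SCM versus MM is safe.** This stands. A reader might infer that the comparison is biased without a baseline. Randomisation protects it, and a baseline score would only add precision.
- **Mood is measured before treatment by other means.** This stands in part. K6, a primary outcome covering depressive mood and anxiety, is taken at baseline and posttreatment in all arms. The relaxation items have a value before the first meditation. The gap is confined to these two scales, chiefly positive affect and arousal.
- **A baseline alone gives only an uncontrolled change.** This is right. Within one arm, such a change mixes treatment with regression to the mean and time trends. It is the reason to add the scales at week 4 in the waitlist as well.
- **The percentages are hypothetical.** This is right. They show a range under assumed time courses and do not estimate this trial's loss.

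None of this supplies the missing value. No later analysis plan can recover a measurement that was not scheduled.

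**Conclusion.** The point holds for these two scales. Change from before treatment cannot be computed on PANAS or the Affect Grid in any arm, and a week-1 reference would hide first-week benefit. Week 4 minus week 1 recovers between 0% and 86% of the week-4 effect for PANAS, and between 0% and 75% for a momentary Affect Grid. These ranges rest on three assumed time courses, on PANAS acting as a week average, and on the Affect Grid being momentary, which the article does not state.

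The consequence is limited to the weekly affect measures. The primary outcomes and listed secondary outcomes have baseline values and are untouched, and the randomised comparison of SCM with MM at weeks 3-4 remains valid. This is a cheap improvement to the schedule and does not threaten the trial's main conclusions.

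**What to change.** **Schedule.** Add PANAS and the Affect Grid (20 + 1 = 21 items) to the existing baseline and week-4 questionnaires in all arms, and tick those cells in Table 1. State that the baseline form in SCM and MM, and the week-4 form in the waitlist, are to be answered before that person's first meditation. This needs saying because Participant Timeline sends the instruction to start the app together with those forms.

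**Analysis.** Use the baseline score as reference and covariate. Use the week-4 scores for a randomised comparison of SCM and MM with the waitlist. For SCM versus MM, the week-2 score may serve as an additional reference.

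**If the data are already in.** The Abstract reports that data collection is complete. Where these values were not collected, state that no pre-course affect score exists. Do not label week 1 a baseline, do not report drift from week 1 to week 4 as a treatment effect, and limit affect conclusions to the randomised SCM versus MM comparison.

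**Cost.** There would be 21 short items at two time points on forms that participants already receive, so slightly more questionnaire burden. The reporting changes need no further data collection.

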### Statistical Methods

#### Primary Outcome

The intention-to-treat approach involving participants who have completed pretreatment and posttreatment assessments will be used to test the effectiveness of the active arms compared to the waitlist group. To examine preintervention and postintervention changes and pre-post differences between the groups, the results of the assessment questionnaires will be analyzed using repeated measures ANOVA. The statistical significance level is set at *P*<.05 for all statistics. Analyses will be performed using SPSS (IBM Corp) and R (R Foundation for Statistical Computing).

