#### Other Analyses

An interim analysis will be conducted once half of the planned number of participants have completed the intervention period. The interim analysis will primarily examine the feasibility, including dropout rates, and the trial may be discontinued if the dropout rate is higher than expected. Multivariate analysis will be conducted to test the effects of the interventions, adjusting for estimated predictors or confounding variables, and multilevel linear regression will be performed.

Following the intention-to-treat principle, the analyses will include data from all participants. Web-based self-care interventions are often associated with higher dropout rates and lower rates of continued implementation [86]. In their study, Farvolden et al [87] reported that only 12 of 1161 participants (approximately 1%) completed a 12-week web-based panic disorder self-help program in its entirety. Similarly, Hasselberg and Rönnlund [83] conducted a 2-week web-based program targeting mindfulness and self-compassion and reported that 33% of the participants stayed in the program until the end. Therefore, even if self-care app activities are minimal, participants will be considered to have completed the course and will be included in the analysis if each questionnaire is answered. The patterns of missing values will be examined and, when applicable, replaced with suitable statistical methods.

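### The primary analysis is labelled intention-to-treat but keeps only participants who answered both questionnaires, and it contradicts the protocol's own statement that all participants are analysed

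*Protocol article*

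**What the plan says.** Statistical Methods, Primary Outcome, sets the population and the model for the primary comparison: "The intention-to-treat approach involving participants who have completed pretreatment and posttreatment assessments will be used", and "the results of the assessment questionnaires will be analyzed using repeated measures ANOVA".

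Statistical Methods, Other Analyses, gives a different population: "Following the intention-to-treat principle, the analyses will include data from all participants". Later in that paragraph, participants with minimal app use "will be included in the analysis if each questionnaire is answered". Its closing sentence says that missing values will be replaced where applicable by suitable methods, and names none. The section also mentions adjusted analyses and multilevel linear regression, but not as the primary analysis.

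Sample Size plans for loss: "Expecting approximately 40% attrition based on similar previous studies".

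Participant Timeline and the Allocation section place assignment directly after consent and screening. The baseline questionnaire is e-mailed after that. Data Collection and Management counts non-response to a questionnaire as dropout.

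**The concern.** Intention-to-treat analyses everyone in the arm to which they were allocated. A set defined by having answered two questionnaires, both sent after allocation, is selected on events after randomisation. If the reasons for answering differ between arms, the groups compared are no longer the randomised groups.

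Such a difference is plausible here. The trial is open-label, and the Blinding section accepts that participants can infer their group. The active arms are asked for daily meditation with daily and weekly assessments, while the waitlist arm only waits.

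The rule governs both primary outcomes, psychological distress and work performance. If it is followed as written, a complete-case result would be published as intention-to-treat. The sentence on replacing missing values does not repair this, because a set that requires both assessments has no missing assessment left to replace.

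**Working it through.** **1. The two rules side by side**

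| Section | Who is analysed |
|---|---|
| Primary Outcome | Participants with both pretreatment and posttreatment assessments |
| Other Analyses, opening of the paragraph | All participants |
| Other Analyses, later in the paragraph | Participants who answered the questionnaires, whatever their app use |

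The first and third rows agree with each other, and the second contradicts both. Classical repeated measures ANOVA with two time points needs both scores per person, so it enforces the first row.

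**2. The plan's own sample size**

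Inputs from Sample Size: "weak interaction effects (Cohen *F*=0.15) based on previous research [81", correlation 0.5, three groups, two times, and "To achieve 80% power, 37 participants are required in each arm (SCM, MM, and control". From Primary Outcome: "The statistical significance level is set at *P*<.05 for all statistics".

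- Noncentrality: λ = f² × N × m / (1 − ρ) = 0.0225 × 111 × 2 / 0.5 = 9.99, with 2 and 108 degrees of freedom.
- Power at N = 111 is 0.803, and 111 is the smallest N that reaches 80%. So 37 per arm reproduces.
- Attrition: 111 / 0.6 = 185, so 200 is enough. 200 × 0.6 = 120 analysed gives power 0.836.

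The sample size is therefore not at fault. It was planned for a set reduced by 40%, which fits the responder set and not the all-participants statement.

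**3. How many could be excluded**

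- 200 × 0.4 = 80.
- With the 375 reported as enrolled in Results, and the same rate assumed: 375 × 0.4 = 150.

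**4. Responder effect against all-randomised effect**

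Let non-responders gain a fraction k of the responders' effect. The all-randomised effect is then (0.6 + 0.4k) times the responder effect. The value of k is an assumption. The last column takes an illustrative responder effect of 0.30 SD.

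| k | Overstatement, 1/(0.6 + 0.4k) | All-randomised effect |
|---|---|---|
| 0 | 1.67 | 0.18 SD |
| 0.5 | 1.25 | 0.24 SD |
| 1 | 1.00 | 0.30 SD |

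**5. No true effect, dropout depending on baseline distress**

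Assumed: 67 randomised per arm, 60% retained in each arm, pre-post correlation 0.5. The slope is the log-odds of dropout per SD of baseline distress. The results are simulated, for the unadjusted change score.

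| Slope, active / waitlist | Bias | Pairwise type I error |
|---|---|---|
| Equal in both arms | 0.00 SD | 5.0% |
| 1 / 0.5 | 0.07 SD | 6.2% |
| 0.5 / 0 | 0.09 SD | 6.7% |
| 1 / 0 | 0.16 to 0.17 SD | 11% to 12% |

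Hand check of the last row: with about 40 analysed per arm and a change SD of √(2 × (1 − 0.5)) = 1, the standard error is √(1/40 + 1/40) = 0.224. The shift is 0.165 / 0.224 = 0.74 standard errors. P(Z > 1.22) + P(Z < −2.70) is about 0.115.

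Direction: if the more distressed leave the active arm, those who remain start low and regress upward, so the active arm looks worse.

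**6. No true effect, unequal attrition related to improvement**

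Assumed: 50% loss in the active arm against 20% in the waitlist arm, with a correlation of 0.2 to 0.4 between staying and improving. The spurious benefit is 0.09 to 0.18 SD in favour of the active arm. At 45% against 30% it is 0.04 to 0.09 SD, and with equal attrition it is zero. So the direction depends on the mechanism.

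**The case against.** Several points on the other side stand.

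- **The 40% is a planning figure.** It is not observed, and it is not split by arm or questionnaire. Other Analyses describes one of the studies cited for it in terms of staying in the programme, and leaving the programme is not the same as failing to answer a questionnaire. Reminders and a gift card scaled to participation may raise response. A reader might infer that 40% of those randomised will be lost. The documents support only that this is the loss planned for.
- **The set is not a treatment-completer set.** Participants who barely use the app stay in their arm if they answer, which is sound for adherence. A reader might infer a per-protocol effect, but selection here is on questionnaire response.
- **Inflated benefit is not shown.** The 1.67-fold figure is the extreme in which non-responders gain nothing. The type I error near 12% needs baseline-dependent dropout in the active arm alone, and it then works against the intervention. It falls to 5% when the mechanism is the same in both arms.
- **A mixed model or multiple imputation does not cure everything.** Both assume data missing at random. In the baseline-dependent case, complete-case ANCOVA adjusted for baseline is also unbiased (bias 0.00, type I error 5.1%), so part of that problem lies in the unadjusted change score.
- **This is a condensed article.** Imputation details may properly sit in an analysis plan that is not shown, and multilevel regression is already listed among the other analyses.

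None of this removes the defect. The article does more than stay silent: it states a population for the primary analysis, gives it the wrong name, and contradicts it in the same chapter. Multilevel regression listed as another analysis does not change the stated primary one.

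**Conclusion.** The point holds. As written, the primary analysis is a complete-case analysis of questionnaire responders under an intention-to-treat label, and Primary Outcome and Other Analyses cannot both be followed. This rests on the text alone and needs no assumption about dropout.

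The size is conditional. Up to 80 of 200 randomised participants would be excluded at the planning rate. The overstatement runs from none to 1.67-fold as the non-responders' gain goes from equal to nil. With no true effect and baseline-dependent dropout, the bias runs from 0 to 0.17 SD and the pairwise type I error from 5% to about 12%. These ranges rest on the assumed mechanisms, a correlation of 0.5 and 60% retention. The documents determine neither the size nor the direction of any bias that will occur. The stated sample size reproduces and is not part of the problem.

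The correction should be made before the arms are compared.

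**What to change.** 1. Reconcile Primary Outcome with Other Analyses: define the primary set as all randomised participants in their allocated arm, and delete the wording that equates intention-to-treat with having both assessments.
2. Replace the repeated measures ANOVA with one named primary method. Either use a likelihood-based mixed model (arm by time) on all available scores, or multiple imputation by arm followed by baseline-adjusted ANCOVA. Use the screening K6 in either. It is collected before randomisation, so it is known for everyone randomised, including those who never answer the baseline questionnaire.
3. Keep the both-questionnaires analysis as a sensitivity analysis, labelled complete-case.
4. Because the new primary analysis still assumes missing at random, add a delta-adjusted sensitivity analysis over a stated range of less favourable outcomes in non-responders.

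The cost is a change of wording and modest extra programming in SPSS or R, both already named. No new data are needed.
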